### Safety assessment and monitoring

NMES intervention will be carried out strictly based on the instrument operation specifications and implemented by two physiotherapists who have completed operation training. Patients will be informed of the potential adverse events of NMES and sign an informed consent form. Adverse events may occur during treatment: mean arterial blood pressure < 65 mmHg, 40 bpm < heart rate < 130 bpm, SpO_2_ < 88%, skin redness, skin burns, skin blisters, pain, myocardial ischemia, and arrhythmia. The NMES group will complete NMES therapy under the supervision of a physiotherapist. During treatment, any patient discomfort will be dealt with immediately (reduce the intensity of electrical stimulation or stop the intervention). The research team will judge the severity of adverse events and analyze the correlation with the intervention. Patients who suffer harm or complications caused by the intervention will receive medical treatment at the Second Affiliated Hospital of Chongqing Medical University free of charge. All serious adverse events will be reported to the ethics committee within 48 h.

Based on the sequential study design, the primary outcome will be analyzed when 50% of participants (40 participants) have randomly enrolled to complete the intervention and data collection. An independent statistician who is blinded to the intervention process will be responsible for performing the data analysis. Type I error statistical analysis will be performed using the Pocock approach with *α* = 0.05. The interim analysis results will be reported to the data monitoring committee (DMC). The DMC will access all data and discuss to decide whether the trial should be continued, modified, or halted earlier than intended.

The data monitoring committee (DMC) will comprise intensive care physicians, rehabilitation physicians, rehabilitation therapists, and statistical experts. DMC members are independent of the sponsor and competing interests. The DMC is mainly charged with safety monitoring and the application of statistics. The DMC will monitor adverse reactions in the study to avoid increasing the risk to the patients. In addition, the DMC will review the data and monitor the quality of the trial conduct (protocol compliance, enrollment status, dropout rate of subjects, and data completeness) and assist the sponsor in deciding whether to terminate the trial early or modify the trial protocol. The DMC will check the quality and plausibility of the data every 2 months.

The adjustment plan of the research protocol (eligibility criteria, intervention plan and process, outcomes, and analyses) will be discussed by the research team. The revised protocol will be submitted to the ethics research committee (the committee) and the institutional review board (the board) of the Second Affiliated Hospital of Chongqing Medical University. For the quality of the study, any modifications to the protocol will be reviewed by the committee and the board.

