### Data collection and statistical analysis

Two trained evaluators will collect baseline data, outcomes, and follow-up data. Participant trial data will be recorded through the case report form. Participants will be informed of follow-up visits after discharge from the hospital, and follow-up data will be obtained through telephone questionnaires or home visits. Two investigators will check the case report form twice to ensure accuracy and completion and record the data of the case report form into the Excel file with double-check.

All participants can withdraw from the trial at any time. If participants terminate the trial or deviate from the intervention protocol, the investigators will record the trial data from the participant’s last intervention and report the reason for withdrawal.

The SPSS 26.0 software (IBM SPSS, Chicago, IL) was applied to analyze the baseline characteristics and outcomes between the two groups. *x̅* ± s will represent continuous variables that conformed to the normal distribution, and the *t* test will compare the differences between the two groups. The Mann–Whitney *U* test will be applied if continuous variables are not normally distributed. Categorical variables will be expressed as frequency (percentage, %), and the chi-square test will be used to compare the differences between the two groups. Effect estimates will be provided with corresponding 95% confidence intervals, and *P* values ≤ 0.05 will be considered significant. Aiming to preserve the unique benefit of randomization, regardless of whether that participant received the allocated intervention, the principles of intention-to-treat analysis will be used. All randomized participants will be included in the analyses, and data will be analyzed in the group in which the participants were originally randomized. All available data from the NMES group that was originally randomized will be analyzed as an intervention group, including participants from the NMES group who do not complete the NMES intervention or even do not receive NMES intervention. Similarly, all available data from the control group that was originally randomized will be analyzed as the control group, including any who receive the NMES intervention. Multiple imputation (MI) using the mice package in R will be applied to analyze the missing data.

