### Ethics and dissemination

The study protocol was approved by the Hospital Research Ethics Committee of Chongqing Medical University on December 30, 2022 (approval no. 2022–301). This protocol was designed on December 30, 2022, with the version of V2.0. The study has been registered with the China Clinical Trial Center with the registration number (no. ChiCTR2300068995). Two researchers will be responsible for signing the informed consent of the participants. All participants will be informed about the benefits and risks of this trial and sign the informed consent by strictly voluntary consent. Participants can withdraw from the study at any time.

The patient’s data will be kept confidential, and only the researchers who manage the data will have access. The grouping information before the trial, informed consent, and the case report form will be kept by two researchers. Among them, two researchers will enter the paper version of the case report form data into an Excel file for preservation and encryption. Only two researchers will have access to the file. The patient’s paper case report form will be sealed in an envelope and stored in the locked file cabinet of the Department of Critical Care Medicine, the Second Affiliated Hospital of Chongqing Medical University. Except in the case of unblinding, only two investigators had access to patient information. According to the medical archive preservation rules and the principles of Good Clinical Practice (GCP), these data will be kept for at least 5 years and be used only for this study.

Participants and the public will not directly participate in the design and implementation of the study. Considering the patient’s privacy, the data will not be released directly to the public, but the protocol and results will be released. Meanwhile, the results of the experimental study will be presented and discussed at academic conferences, and experimental results will be published in peer journals.

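### The heart-rate item in the adverse-event list is printed the wrong way round: it describes rates between 40 and 130 bpm instead of rates outside those limits

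*Protocol article*

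**What the plan says.** Safety assessment and monitoring introduces a list of adverse events that may occur during treatment. Its first two items are printed as "mean arterial blood pressure < 65 mmHg, 40 bpm < heart rate < 130 bpm". The rest of the list is "SpO_2_ < 88%, skin redness, skin burns, skin blisters, pain, myocardial ischemia, and arrhythmia". Three items therefore carry numeric vital-sign limits: mean arterial pressure, heart rate and oxygen saturation.

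The same section has the research team grade the severity of adverse events and assess their relation to the intervention. The data monitoring committee is given the monitoring of adverse reactions.

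On recording, Data collection and statistical analysis states: "Participant trial data will be recorded through the case report form". Ethics and dissemination refers to a fuller document: "This protocol was designed on December 30, 2022, with the version of V2.0". Neither the form nor that version is available here. No other section of the article gives a heart-rate limit.

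**The concern.** A list of adverse events should name abnormal states. The blood-pressure and saturation items do: each is met when the value falls below an acceptable floor. The heart-rate item is met when the rate lies within its two limits, so as printed it describes the acceptable state.

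What is at stake is safety recording. If the line were carried literally into a case report form or a data check, it would flag ordinary heart rates and miss bradycardia and tachycardia beyond the limits, except where these were recorded as arrhythmia. The events that the research team grades and the data monitoring committee monitors would then be wrong on this item. Efficacy results are not at stake, and no effect on blinding is claimed.

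**Working it through.** No sample-size or power figure is involved, so there is no figure of the plan's to reproduce. The check is one of logic.

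**Inputs**, all from Safety assessment and monitoring:
- mean arterial pressure: event if below 65 mmHg
- heart rate (HR): event if 40 < HR < 130 bpm
- oxygen saturation: event if below 88%

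**Step 1: direction of each item.** Mean arterial pressure and saturation are each met by abnormally low values. Heart rate is met by values in the open interval from 40 to 130. One of the three runs the opposite way.

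**Step 2: compare the printed item with the out-of-range form on the same limits** (HR < 40 or HR > 130).

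| HR (bpm) | Printed item: event? | Out-of-range form: event? |
|---|---|---|
| 35 | no | yes |
| 40 | no | no |
| 41 | yes | no |
| 80 | yes | no |
| 129 | yes | no |
| 130 | no | no |
| 131 | no | yes |
| 150 | no | yes |

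The two forms give opposite answers at every whole-number rate except exactly 40 and exactly 130, which neither flags. Over 20 to 200 bpm, a range chosen only for illustration, there are 200 − 20 + 1 = 181 whole-number rates. The printed item flags 129 − 41 + 1 = 89 of them. The out-of-range form flags 20 (20 to 39) plus 70 (131 to 200), which is 90. The forms disagree at 89 + 90 = 179 rates and agree at 2. This count only shows that one form is, but for its endpoints, the complement of the other. It does not estimate how many events would be misrecorded.

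**Step 3: can another reading rescue the line?** If the list were meant as conditions for continuing stimulation, the heart-rate interval would be right. The blood-pressure and saturation items would then be reversed, and the sentence would still mix the two directions. The introduction also says plainly that these are adverse events. The expression is a complete chained inequality with both limits, both units and both signs present, so garbled text is an unlikely explanation.

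**The case against.** The strongest reply accepts that the line is wrong and disputes its weight.

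- **The list is descriptive.** No stopping rule, dose change or reporting duty is tied to the heart-rate figure. Reducing or stopping stimulation is triggered by patient discomfort, and reporting to the ethics committee within 48 h applies to serious adverse events. This stands. It means the line should not be called a stopping threshold. It remains a numeric criterion for an adverse event.
- **Nobody would apply it literally.** It would make a normal heart rate an event in nearly every session. A physiotherapist supervises treatment, and a data monitoring committee that includes intensive care physicians checks data plausibility every 2 months. This largely stands and is the main reason to rate the point minor.
- **Arrhythmia and myocardial ischaemia are listed separately.** Some extreme rates could be recorded there. This stands in part: the arrhythmia item has no numeric limit, so it does not replace a heart-rate criterion.
- **The harm depends on documents not shown.** The article describes a paper form checked twice by investigators and no automated range check, and the full protocol may have the limits right. This also stands: whether the slip reached working documents is unknown.

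None of this makes the printed line correct. Nor is it a detail that an article may leave to a fuller document, because the article prints the criterion and prints it reversed.

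**Conclusion.** The concern holds, as a minor wording error in a safety definition. One of the three numeric vital-sign items is reversed, and as printed it gives the opposite of the evident intention at every whole-number rate except the two limits themselves.

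The conclusion assumes that the intended criterion is the out-of-range one on the printed limits. The neighbouring items and the introduction to the list support this, but the article does not state it. The number of events affected cannot be derived. Sample size, outcomes, type I error and the efficacy analysis are unaffected.

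**What to change.** Restate the item as an out-of-range criterion. On the printed limits this is heart rate < 40 bpm or > 130 bpm. The clinical team should confirm those limits and say whether exactly 40 and exactly 130 bpm count as events.

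Then check that the full protocol, the case report form and any safety reports already issued use the corrected direction. If any carried the printed form, review the heart-rate entries made under it.

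The cost is one corrected line and a check of wording, with no change to sample size, outcomes or analysis.

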### Ethics and dissemination

The study protocol was approved by the Hospital Research Ethics Committee of Chongqing Medical University on December 30, 2022 (approval no. 2022–301). This protocol was designed on December 30, 2022, with the version of V2.0. The study has been registered with the China Clinical Trial Center with the registration number (no. ChiCTR2300068995). Two researchers will be responsible for signing the informed consent of the participants. All participants will be informed about the benefits and risks of this trial and sign the informed consent by strictly voluntary consent. Participants can withdraw from the study at any time.

The patient’s data will be kept confidential, and only the researchers who manage the data will have access. The grouping information before the trial, informed consent, and the case report form will be kept by two researchers. Among them, two researchers will enter the paper version of the case report form data into an Excel file for preservation and encryption. Only two researchers will have access to the file. The patient’s paper case report form will be sealed in an envelope and stored in the locked file cabinet of the Department of Critical Care Medicine, the Second Affiliated Hospital of Chongqing Medical University. Except in the case of unblinding, only two investigators had access to patient information. According to the medical archive preservation rules and the principles of Good Clinical Practice (GCP), these data will be kept for at least 5 years and be used only for this study.

Participants and the public will not directly participate in the design and implementation of the study. Considering the patient’s privacy, the data will not be released directly to the public, but the protocol and results will be released. Meanwhile, the results of the experimental study will be presented and discussed at academic conferences, and experimental results will be published in peer journals.

## Discussion

To the best of our knowledge, this is the first study to focus on functional recovery, aiming to explore the effect of early NMES intervention on SAP with ARDS. The changes in muscle mass, diaphragm function, multiple organ dysfunction, and quality of life will be demonstrated after receiving 7 days of NMES intervention. In addition, the effect of early NMES intervention in the 1st month, 3rd month, and 6th month after discharge will be determined through follow-up.

ARDS is a common early complication of SAP, occurring 2–7 days after pancreatic inflammation. Furthermore, Fei et al. [36] indicated that ARDS increases the mortality rate of SAP in the first week of the disease. To ensure the stability of patients’ lives, critical care treatment is needed. Mechanical ventilation, blood purification, sedation, and analgesia are the supportive care for SAP with ARDS. However, critical care treatment impairs the patient’s physical activity, causing physical function to drop sharply in the early stage. A study of patient quality of life showed that survivors of SAP had significantly reduced SF-36 scores compared with age-matched controls, especially in the domains of social and physical function and general health [37]. Although there is currently insufficient evidence that SAP with ARDS will impair muscle mass, SAP and ARDS are major factors that attenuate muscle mass and reduce quality of life, respectively. Several studies have indicated that severe pancreatitis demonstrates a strong association with myosteatosis and muscle attenuation, which is related to poor survival [38, 39]. Dinglas et al. [40] showed that more than 1/3 of ARDS survivors experienced muscle weakness at hospital discharge, and 5-year follow-up outcomes after ARDS onset showed that patients with lower MRC sum scores were associated with higher mortality. The results of the 6-min walk test (6MWD) and SF-36 measures demonstrate that ARDS patients have reduced exercise capacity and quality of life in the first year [41]. To investigate the protocol for preventing physical function impairment, this trial aims to provide sufficient evidence about the efficacy of early NMES treatment in patients with SAP complicated with ARDS.

Considering the poor ability to participate in physical activities autonomously in early patients with SAP combined with ARDS, we plan to provide NMES intervention for 7 days within 48 h of admission to the intensive care unit. This study designed NMES to be applied in patients’ bilateral quadriceps and tibialis anterior for approximately 60 min/day. To assess the effect of NMES on muscle mass, the MRC scale will be used to evaluate muscle strength. In addition, we collected the changes in the latitude of the patients’ bilateral lower extremities and grip strength [42, 43]. Finally, whether NMES has a positive effect on diaphragm function and multiple organ dysfunction will be further explored through this trial. We will follow-up on quality of life to determine the sustained effect of NMES on patients with SAP and ARDS.

Although there are not enough studies on the efficacy of NMES for SAP with ARDS in the current era, recent evidence has shown that early NMES can reduce muscle atrophy and outcome measures for postoperative and critically ill patients. Campos et al. reported that compared with the early mobilization group, early NMSE and mobilization intervention improved the functional status score on the first day awake for patients who were mechanically ventilated [25]. A similar small-sample study showed that patients who underwent prolonged mechanical ventilation received NMES on the vastus lateralis and rectus femoris, concluding that the NMES group significantly increased MRC points and prevented decreased limb circumference [44]. To further investigate the therapeutic effect of NMES, we aimed to examine the effects of NMES in SAP patients with ARDS.

In conclusion, this trial compared the effect of early neuromuscular electrical stimulation on patients with SAP and ARDS through a randomized controlled trial, aiming to determine the effects of NMES on muscle strength, diaphragm function, multiple organ dysfunction, and quality of life.

## Data Availability

Not applicable.

## Abbreviations

NMES: Neuromuscular electrical stimulation
AP: Acute pancreatitis
SAP: Severe acute pancreatitis
ARDS: Acute respiratory distress syndrome
ICU: Intensive care unit
MRC: Medical Research Council
APACHE II: Acute physiology and chronic health evaluation II
DMC: Data monitoring committee
